## ROLE OF NITRATE IN HYPOXIC CONDITIONS

NO may also be an important mediator in the adaptation to life in a hypoxic environment. Observational studies of high altitude dwelling humans have shown higher levels of exhaled NO[^65^](#_ENREF_65) and plasma nitrite[^66^](#_ENREF_66) than lowlanders. This cannot be accounted for by increased dietary consumption of nitrate as the average daily consumption studied would have been insufficient to increase plasma levels of nitrate and nitrite significantly[^66^](#_ENREF_66). This suggests such persons adapted to life at altitude have upregulation of endogenous NO that may help them meet this physiological challenge.

In line with studies from sports medicine, comparisons between long-term Tibetan residents and newly acclimatised residents at altitude show lower VO_2max_ in the Tibetan group and higher workload at maximal exercise effort illustrating possible improved exercise efficiency of the Tibetan population[^67^](#_ENREF_67). This suggests a possible causal mechanism related to upregulation of endogenous NO.

Further to this in studies of high altitude sickness, there is a noted association with reduced exhaled NO[^68^](#_ENREF_68) and polymorphisms of endothelial NOS[^69^](#_ENREF_69). This may indicate an adaptive role for NO in the physiological challenge of the hypoxia of altitude by reducing the oxygen cost of physical activity. In support, enhancing dietary nitrate has been demonstrated to reduce the oxygen cost of exercise at a submaximal workload in an hypoxic environment[^70^](#_ENREF_70)^,^ [^71^](#_ENREF_71). Masschelein et al. (2012)[^70^](#_ENREF_70) tested 15 healthy volunteers via submaximal workload cycle ergometry at both normoxia and in hypoxic conditions (11% oxygen) after loading with nitrate supplementation or placebo control. VO_2_ was notably lower at both rest and during submaximal exercise after nitrate supplementation than control, and was associated with improved tissue oxygenation index and lower rate of muscle oxygen extraction as assessed by near infrared spectroscopy[^70^](#_ENREF_70). This effect seems to be independent of increased muscle blood flow using indirect measures via NIRS, suggesting that upregulation of NO has effects beyond simply that on the vasculature[^70^](#_ENREF_70). Nitrate supplementation has also been shown to attenuate the perturbation in muscle metabolism seen in hypoxia. Vanhatalo et al. (2011) tested 9 healthy subjects via incremental knee extension exercise to the limit of tolerance, showing prior treatment with nitrate significantly increased the exercise time and improved the kinetics of phosphocreatine recovery post exercise.

These studies are clearly of interest in the study of chronic respiratory disease such as COPD, which is frequently associated with tissue hypoxia and ventilatory limitation. In those with chronic lung disease simply performing the activities of daily living requires energy that represents a high proportion of VO_2max_, thus any intervention that reduces the oxygen cost in conditions where oxygen supply is limited has the potential to improve functional abilities and quality of life in this patient population. Improving skeletal muscle blood flow and the efficiency of energy metabolism in working tissues has significant potential to improve physical activity, and potentially via a cost-effective simple nutritional intervention.

Pre-existing clinical studies have been undertaken in patients with peripheral arterial disease where oxygen delivery is unable to meet the demands of metabolically active tissue of the legs during walking; leading to the development of claudicant pain that then limits further exertion. Kenjale et al. (2011)[^72^](#_ENREF_72) studied 9 patients with peripheral vascular disease in an open-label, randomised, cross-over trial of nitrate supplementation versus placebo. The supplementation of nitrate by beetroot juice administration has been shown to improve both walking distance and time before the onset of claudicant pain, by 18% and 17% respectively, in an incremental walking test[^72^](#_ENREF_72). This is associated with lower gastrocnemius fractional oxygen extraction as assessed by near infrared spectroscopy[^72^](#_ENREF_72) indicating improved energy efficiency.

## APPLICATION OF NEAR INFRARED SPECTROSCOPY (NIRS)

NIRS provides a semi-quantitative non-invasive measure of tissue oxygenation status[^73^](#_ENREF_73). NIR light penetrates biological tissues and allows the detection of changes in light-absorbing molecules such as haemoglobin in humans. The intensity of incident and transmitted light is used to estimate concentration changes from the resting baseline for oxygenated (HbO_2_), deoxygenated (HHb) and total tissue haemoglobin/myoglobin (THb) in the microvasculature of the muscle.

Changes in tissue oxygenation status can be measured to estimate the fractional oxygen extraction. The HHb signal is considered to be a surrogate of microvascular oxygen extraction as it is little influenced by changes in blood volume[^74^](#_ENREF_74), thus its amplitude can provide a non-invasive index of fractional oxygen extraction. The ratio of oxyhaemoglobin to total haemoglobin can also be studied to allow measurement of the tissue oxygenation index (TOI). Studies have demonstrated reduced fractional oxygen extraction as assessed by NIRS during exercise in both healthy adults receiving nitrate supplementation[^37^](#_ENREF_37) and in adults diagnosed with peripheral arterial disease[^72^](#_ENREF_72).

# 2. STUDY OBJECTIVES

The purpose of this study is to investigate the effects of an acute administration of beetroot (BR) juice versus placebo beverage ingestion on plasma NO_2_^-^ levels, blood pressure, exercise tolerance and fractional oxygen extraction.

The following hypotheses are to be tested:

1) BR would increase plasma NO_2_^-^ levels (a biomarker of NO production and availability)

2) BR would increase cycling time to exhaustion at a fixed workrate (70% peak)

3) BR will reduce oxygen consumption during equivalent exercise (area under VO_2_ curve to isotime)

4) BR would reduce fractional oxygen extraction of the quadriceps as assessed by NIRS

# 3. STUDY DESIGN

The study is a randomised, double-blind, cross-over, placebo-controlled trial. 25 patients with COPD will be randomised to receive nitrate-rich beetroot juice or placebo as a bolus dose 3 hours prior to endurance cycle ergometry, and then cross-over to the other intervention.

### 3.1 STUDY OUTCOME MEASURES

*Primary endpoint* will be an increase in time to exhaustion at 70% peak workload on a cycle ergometer.

*Secondary endpoints* will be:

1. Area under VO_2_ curve to isotime (VO_2_) during endurance cycle ergometry;
2. Fractional oxygen extraction of quadriceps muscle as assessed by NIRS.
3. Mitochondrial DNA levels
4. Branched chain amino acid levels

# 4. PARTICIPANT ENTRY

### 4.1 PRE-RANDOMISATION EVALUATIONS

Patients will have a clinical and spirometric diagnosis of COPD.

### 4.2 INCLUSION CRITERIA

Patients will need to have a clinical and spirometric diagnosis of COPD, GOLD stage II-IV.

### 4.2 EXCLUSION CRITERIA

Clinically unstable patients (within one month of exacerbation), significant comorbidity limiting exercise tolerance, significant renal impairment (estimated glomerular filtration rate (eGFR) <50 ml.min^-1^), hypotension (systolic blood pressure <100 mmHg), pregnancy, use of nitrate based medication, other reason for benefit from nitrate supplementation (ischaemic heart disease, peripheral arterial disease), use of long-term oxygen therapy.

### 4.3 WITHDRAWAL CRITERIA

Patients will be withdrawn from the study if: they have a significant adverse event or if they withdraw their consent for participation. If patients withdraw their consent their data will be destroyed.

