## 6.2 LOSS TO FOLLOW-UP

Efforts will be made to contact patients by post and telephone and be reference to their GPs. Where it is not possible to contact them their vital status will be reviewed by referring to the ONS database 3 months after the planned end of their study participation.

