# 7. STATISTICS AND DATA ANALYSIS

The primary endpoint will be the change in time to exhaustion in a fixed workload cycle ergometer test. This is a validated endpoint in COPD, having been previously in studies of therapeutic interventions[^77^](#_ENREF_77).

Data and all appropriate documentation will be stored for a minimum of 10 years after the completion of the study, including the follow-up period.

As this is a pilot study a pragmatic sample size of 25 has been selected as offering a good chance of identifying a clinically meaningful effect.

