## 9.2 CONSENT

Consent to enter the study must be sought from each participant only after a full explanation has been given, an information leaflet offered and time allowed for consideration. Signed participant consent should be obtained. The right of the participant to refuse to participate without giving reasons must be respected. After the participant has entered the trial the clinician remains free to give alternative treatment to that specified in the protocol at any stage if he/she feels it is in the participant’s best interest, but the reasons for doing so should be recorded. In these cases the participants remain within the study for the purposes of follow-up and data analysis. All participants are free to withdraw at any time from the protocol treatment without giving reasons and without prejudicing further treatment.

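### Section 4.3 orders destruction of all data when consent is withdrawn, including outcomes and adverse events already collected, and this conflicts with the 10-year retention rule in Section 7

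*Protocol*

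**What the plan says.** Protocol Section 4.3 gives two grounds for leaving the study: "Patients will be withdrawn from the study if: they have a significant adverse event or if they withdraw their consent for participation". It then adds, for the second ground only: "If patients withdraw their consent their data will be destroyed".

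Section 7 sets the retention rule: "Data and all appropriate documentation will be stored for a minimum of 10 years after the completion of the study, including the follow-up period". It names no exception.

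Section 9.2 deals with two neighbouring situations. The first is a clinician giving a different treatment in the participant's interest: "In these cases the participants remain within the study for the purposes of follow-up and data analysis". The second is stopping the intervention: "All participants are free to withdraw at any time from the protocol treatment without giving reasons and without prejudicing further treatment". Neither sentence says what happens to data when consent to the study itself is withdrawn.

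Sections 3 and 6 fix the design. It is a cross-over in 25 patients, with one drink and one endurance ride at each of visits 3 and 4, at least 7 days apart, and serial blood samples at both visits.

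**The concern.** The destruction rule is mandatory. It is not confined to identifiers or to future data, it does not depend on a request for erasure, and it does not spare adverse events. It acts after randomisation and can act after dosing, after a ride to exhaustion and after blood sampling. An analysis plan cannot repair this later, because destroyed records cannot be analysed.

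Three things are at stake:

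- **Safety data.** An adverse event disappears if the patient who had it then withdraws consent.
- **Patient accounting.** Randomised patients can no longer be described by sequence and period.
- **The treatment comparison.** Precision is lost. If the decision to withdraw depends on how the patient tolerated the drink or performed on the ride, the estimate is biased as well.

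The rule also leaves the trial team with two instructions, destroy and retain, that cannot both be followed for the same patient.

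**Working it through.** **1. The rules side by side**

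| Section | Who is covered | What is ordered for the data |
|---|---|---|
| 4.3, second ground | Patient withdraws consent | Destroy, no exception |
| 4.3, first ground | Patient with a significant adverse event | Withdrawn from the study; nothing said about destruction |
| 7 | All trial data | Keep at least 10 years, no exception |
| 9.2, alternative treatment | Clinician changes treatment | Remains in follow-up and analysis |
| 9.2, withdrawal | Participant stops protocol treatment | Nothing said |
| 6.2 | Patient cannot be contacted | Check of vital status |

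Only the first and third rows give opposite orders for the same patient. The rows for 9.2 and 6.2 cover other groups.

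There is still an unclear boundary. The intervention is a single drink at each of two visits. A patient who declines the second drink could be recorded as stopping protocol treatment (9.2) or as withdrawing consent (4.3). Under the first label nothing orders destruction; under the second the data are destroyed. The protocol gives no criterion for choosing.

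**2. What the rule removes, by time of withdrawal**

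| Consent withdrawn | Within-patient difference without the rule | Removed by the rule |
|---|---|---|
| After randomisation, before visit 3 | None | Baseline data, place in the accounting by sequence |
| After visit 3, before visit 4 | None | First-period outcome, first-period adverse events, accounting |
| After visit 4 | Yes | The full pair, all adverse events, accounting |

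A patient who leaves before visit 4 has no within-patient difference whether or not the record is destroyed. Destruction therefore costs a paired analysis something only in the last row.

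**3. Size**

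The protocol calls 25 a pragmatic number and states no alpha, power, effect, SD or withdrawal rate, so it has no figure to reproduce. The calculations below are illustrations.

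*Share per patient:* 1/25 = 4%.

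*Safety (applies only if the patient with the event also withdraws consent):*
- One event in 25: 4%. The exact lower limit is 1 − 0.975^(1/25) = 0.1%. The upper limit U solves (1−U)^25 + 25U(1−U)^24 = 0.025, giving 20.4%.
- After destruction, none in 24: 0%, with upper limit 1 − 0.025^(1/24) = 14.2%.

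*Precision (applies only to k patients who withdraw consent after both rides):* the standard error of the mean paired difference is multiplied by √(25/(25−k)). The power column assumes a two-sided 5% paired t-test and an effect (0.584 SD of the paired difference) that gives 80% power at n = 25.

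| k | n | SE multiplier | Power |
|---|---|---|---|
| 0 | 25 | 1.000 | 80% |
| 1 | 24 | 1.021 | 78% |
| 3 | 22 | 1.066 | 74% |
| 5 | 20 | 1.118 | 70% |

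*Bias, extreme bound (same restriction):* 200,000 simulated trials used normal paired differences, no true effect, and deletion of the k lowest nitrate-minus-placebo differences. For k = 1, 3 and 5 the mean shifts by 0.08, 0.22 and 0.34 SD, and the two-sided 5% test rejects in about 8%, 24% and 46% of trials. This is the worst possible pattern of loss and not a forecast. If withdrawal is unrelated to outcome, the shift is zero and only the precision loss remains.

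**The case against.** The strongest defence has four parts.

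- **A specific rule overrides a general one.** Section 4.3 can be read as an exception to Section 7 for one group of patients. That is a reasonable reading, but Section 7 does not state it. Even if it is accepted, it settles only the conflict: outcomes and adverse events would still be destroyed.
- **The rule may be a deliberate promise to participants.** The study has ethics approval, and the consent pages are not in the copy reviewed. This stands as a reason to honour what enrolled patients were told. It does not require automatic destruction for future patients who have not asked for it.
- **The exposure is small.** Participation is given as 4 weeks, with one dose at each of two visits, the study is rated low risk, and visit 4 is the last visit listed. Few complete pairs are likely to be lost. This stands and limits the efficacy argument. It does not help the first-period and safety data.
- **No withdrawal rate is given.** This also stands: the expected loss cannot be calculated.

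Two stronger readings are tempting, and the documents do not support them. A reader might infer that Section 9.2 contradicts Section 4.3. It does not: its sentence on remaining in the study refers to patients given alternative treatment by the clinician, and the next sentence concerns stopping protocol treatment and promises that further care is unaffected. A reader might also infer that the data of every patient withdrawn for a significant adverse event are destroyed. Section 4.3 attaches destruction to withdrawal of consent alone, so such an event is lost only if that patient also withdraws consent.

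**Conclusion.** The point holds as a badly fixed rule that should be corrected. Section 4.3 removes post-randomisation outcome and safety data irreversibly, and it conflicts with the unqualified retention rule in Section 7. Section 9.2 is compatible with it, although the line between stopping protocol treatment and withdrawing consent needs to be drawn.

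The certain loss for each patient who withdraws consent is the data collected so far, any adverse events, and that patient's place in the accounting by sequence. This assumes that the rule is applied literally to everything held on the patient. A complete pair is lost only when consent is withdrawn after visit 4. Bias in the treatment effect requires in addition that withdrawal is related to tolerance or performance; this is plausible after an exhausting ride, but the documents do not show it. It would therefore be wrong to conclude that the rule makes the efficacy result biased, or to count ordinary dropout before visit 4 as a cost of the rule.

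**What to change.** Replace the last sentence of Section 4.3 with wording such as:

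> When a participant withdraws consent, no further data are collected. Data already collected, including adverse events, are kept and analysed unless the participant specifically asks for their erasure. The number of withdrawals and of erasure requests is reported by sequence and period.

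In the same edit:

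- add to Section 7 that the 10-year retention applies subject to such erasure requests;
- state in Sections 4.3 and 9.2 how stopping protocol treatment is distinguished from withdrawing consent, and how each is recorded;
- align the participant information sheet.

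The cost is a protocol and information-sheet change with an ethics amendment. For patients already enrolled, either the existing promise is honoured or they are asked to re-consent. Some data may still be erased on request, but those losses would then be counted and visible. The change is best made before the next withdrawal, since a destroyed record cannot be recovered.

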# 5. RANDOMISATION AND ENROLMENT PROCEDURE

## 5.1 RANDOMISATION OR REGISTRATION PRACTICALITIES

Patients will be randomly assigned to the order in which they receive nitrate-rich beetroot juice versus placebo. Randomisation will be performed using block randomisation with consecutive numbers linked to identical preparations of placebo or active treatment. The list will be generated by [name], Trust statistician.

## 5.2 UNBLINDING

If necessary this will be done through [name] who will hold an unblinded list.

# 6. ASSESSMENT AND FOLLOW-UP

See appendix for table.

Patients with diagnosed COPD will be approached to consider participation in the study either in clinic or through the department’s research audit database.

Visit 1 -Inclusion/exclusion criteria reviewed including spirometry.

-Consent taken.

-Blood sample for renal function (if not tested in the previous 12 months).

Visit 2 -Baseline medical history and clinical examination including blood pressure, anthropometrics and measurement of body composition.

-Blood withdrawal for analysis.

-Full pulmonary function testing if not performed within 3 months.

-Quadriceps maximal voluntary contraction.

-Activity monitor supplied to wear for one week.

-Questionnaires.

-Incremental cycle ergometry for determination of peak workload and VO_2max_.

Visit 3/4 -Fixed rate, symptom limited cycle ergometry (at 70% peak workload VO_2max_) after dosing with beetroot juice (BR) or placebo (PL) - time to exhaustion measured VO_2_ and fractional oxygen extraction as assessed by NIRS.

-Blood withdrawal at times 0hr (arrival), 3hr (pre exercise), at peak exercise and 15 minutes post exercise (with BR or PL being administered at 0hr).

Subjects will be asked to avoid nitrate-rich foods in the 48hr prior to the day of testing for visits 3 and 4, and to avoid any strenuous exertion in the 24hr preceding period. They will be asked to avoid cooked food for breakfast and eat the same meal prior to both visits 3 and 4 and ensure that caffeine consumption is matched. They will also be asked to avoid use of any mouthwash or chewing gum which removes the oral bacteria responsible for nitrate reductase activity[^23^](#_ENREF_23).

Testing for visits 3 and 4 should occur at the same time of day (+/- 2hr). Subjects will be given a 140ml volume of BR or PL to consume at time 0hr. This volume of BR provides 0.8g nitrate (12.9 mmol).

There is a minimum 7 day washout period between visits 3 and 4.

## 6.1 DETAILS OF ASSESSMENTS

-Blood samples: At visit 1 or 2 patients will have a baseline measurement of their renal function. At visits 3 and 4 serial blood samples will be taken to measure plasma nitrite levels and to measure mitochondrial DNA and branched chain amino acids (a marker of muscle damage)

- Mouth nitrate levels –mouth washings will be frozen and stored for subsequent analysis to measure nitrate levels in the mouth (due to commensal bacteria)

-Fat free mass: Will be determined using bioelectrical impedance analysis by measuring the electrical resistance between the wrist and ankle using a Bodystat 1500 device. This value is dependent on body water content and based on this fat free mass can be calculated using a disease specific regression equation[^75^](#_ENREF_75).

-Lung function: Will be measured in the lung function department of the Royal Brompton Hospital according to international guidelines and with rigorous quality assurance in place with a Jaeger master lab system. Spirometry, gas transfer and plethysmographic lung volumes (TLC, RV, FRC) will also be measured. All lung function tests will be performed with patients taking their usual regular medication.

-Quadriceps strength: Maximum isometric quadriceps force (QMVC) will be measured using the technique of Edwards et al.[^76^](#_ENREF_76) The maximum force generated during at least three maximum voluntary contractions with vigorous encouragement is measured.

- Incremental Cycle ergometry: A symptom limited incremental exercise test will be performed on a cycle ergometer with metabolic measurements collected using a mouthpiece. Following a 2 minute rest period and 2 minutes free cycling workload will increase by 5 Watts every 30 seconds. Measurements will include peak workload, VO_2_, VCO_2_, minute ventilation, respiratory rate and tidal volume.

-Endurance cycle ergometry test at a fixed workload (70% peak workload). Two minutes at rest, 2 minutes free cycle, then at a fixed workload (70% peak watts) until exhaustion. Standardised encouragement will be given and patients will be asked about limiting symptoms.

-Physical activity monitoring: Patients will wear a multiaxial physical activity monitor continually for a week as part of their baseline assessment. This will record step count and physical activity level. The monitor can be returned by post.

## 6.2 LOSS TO FOLLOW-UP

Efforts will be made to contact patients by post and telephone and be reference to their GPs. Where it is not possible to contact them their vital status will be reviewed by referring to the ONS database 3 months after the planned end of their study participation.

